### Outcome measurements

#### Neonatal deaths

We will investigate all neonatal deaths reported by the SS to the Field Implementers or by maternal recall at the final follow-up visit at 42 days postpartum, using standard questionnaires collected by trained staff. We will use this data to calculate estimates of neonatal mortality in both arms from baseline to the end of the intervention period.

#### Verbal autopsy

Trained Field Research Officers will interview caretakers of infants who die in the neonatal period using the World Health Organization (WHO) Standard Verbal Autopsy Questionnaire [15] within one month of the death. Investigators will extract and code the symptoms from both the closed-ended questions and open narratives. We will use physician-certified verbal autopsy method to identify cases of death related to preterm delivery and birth asphyxia using the hierarchical assignment of causes of death. At least two physicians will independently review the data, and they will base their decision on an agreement. Review by a third physician will resolve any discrepancy between the two diagnoses.

#### Birth weight

We will measure birth weight within 24 h of delivery using standard methods with a portable electronic scale. The SS will notify the Field Implementers of any births in their area, and both will visit the mother and her infant within 24 h, although measurements will be accepted up to 72 h after birth.

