### Regular supply of IFA supplements and counselling

Upon receiving the consent icddr,b study staff (Field Implementers or FI) will hand over the first two months of supply of iron-folic acid capsules, each containing 60 mg of elemental iron and 400μg of folic acid. She will also counsel the mother about the benefits of IFA supplements in pregnancy. The SS will then make regular fortnightly visits to the woman until delivery to ensure resupply of supplements, and provide counselling in support of early uptake, continued use, and compliance with the supplementation regime until delivery. This intervention is consistent with the Bangladesh Ministry of Health guidelines.

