### Management and training

Overall around 3920 SS and 100 FI will deliver the intervention, under the supervision of central field supervisory team. There will be one FI for each cluster. The central team will comprise of three research fellows, one medical officer and one research investigator and one BRAC national manager. The field supervision team will comprise of five Field Research Officers and five District Managers. We will train the BRAC village workers and volunteers in sub-district health centres to detect and monitor pregnancies, to maintain pregnancy records, to manage supply and distribution of supplements, communication and counselling skills for behaviour change related to use of iron-folic acid supplements. The central team will train the field team and monitor the process of delivery of the intervention. The BRAC PO will provide technical support to the SK and SS, and will help them resolve any problems through regular meetings in the field.

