### Evaluation

#### Data collection team

A separate team of trained data collectors not involved in the implementation of the intervention will collect data for evaluation. The evaluation team will consist of 135 data collectors, five field supervisors and five field research officers. Each data collector will be responsible for one cluster. We will train the evaluation team over a four-week period, and standardize measurement methods and retrain as needed every six months.

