#### Data collection schedule

The data collectors will visit each woman a total number of six times from the time of enrolment till 42 days after delivery. These visits will be made between 12 and 14 weeks, 20–24 weeks, 28–32 weeks, within 24 h of delivery, 7–10 days after delivery, 38–42 days after delivery (Fig. 2).

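### The article names two different teams for the birth-weight visit, one of which delivers the unmasked intervention; SS death reports add a second, possibly arm-dependent route to the primary outcome

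*Protocol article*

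**What the plan says.** All references are to the protocol article.

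**Who delivers the intervention.** Management and training: "Overall around 3920 SS and 100 FI will deliver the intervention". Under Regular supply of IFA supplements and counselling, the Field Implementer hands over the first capsules and counsels the woman. After that, "The SS will then make regular fortnightly visits to the woman until delivery". Assignment of treatments says that masking is not possible.

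**Birth weight.** The SS tells the Field Implementer of each birth, and "both will visit the mother and her infant within 24 h, although measurements will be accepted up to 72 h after birth". No data collector is mentioned in this section.

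**Neonatal deaths.** The plan investigates "neonatal deaths reported by the SS to the Field Implementers or by maternal recall at the final follow-up visit at 42 days postpartum" and calculates mortality in both arms from these data.

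**Evaluation.** Data collection team: "A separate team of trained data collectors not involved in the implementation of the intervention will collect data for evaluation". Data collection schedule gives this team six visits per woman, the last three being "within 24 h of delivery, 7–10 days after delivery, 38–42 days after delivery". Types of information collected lists both birth weight and neonatal deaths among the items that the data collectors record.

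**Control arm.** The Control section says that pregnancies are found by methods similar to those in the intervention arm, and that women otherwise receive usual BRAC care. It describes no fortnightly SS visits.

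**The concern.** In an unmasked cluster trial, a separate evaluation team is the main protection against outcome data being shaped by people who know the allocation and have promoted the treatment. The article promises that protection in one place and appears to set it aside in another.

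Two outcomes are touched. Low birth weight is a secondary outcome, and both the person weighing and the age of the infant at weighing could differ by arm. Neonatal mortality is the primary outcome, and one of its two case-finding routes runs through staff whose contact with women differs by arm. If ascertainment differs between arms, an intention-to-treat analysis does not correct it, and without a record of who found each death or when each weight was taken, nobody can check it afterwards.

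**Working it through.** **1. Who is at the birth-weight visit.** The Birth weight section names the SS and the Field Implementer. The three evaluation sections name a data collector who is not an implementer, give that person a visit within 24 h of delivery, and list birth weight among the items collected. The two descriptions cover the same measurement in the same window with different staff. The Birth weight section does not state who holds the scale; that the SS or Field Implementer weighs is implied by their being the only staff named.

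**2. What differs by arm.** Fortnightly SS contact until delivery is described for intervention clusters only. Field Implementers number 100, one per cluster, and the trial has 100 clusters, so they appear to work in both arms. The documented contact difference is therefore the SS, and it is antenatal.

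**3. How a birth becomes known.** SS notification is the only birth alert described. The Electronic data collection tool section gives data collectors a list of visits due within seven days but no means of learning that a birth has occurred. Even if a data collector does the weighing, the time from birth to weighing, anywhere up to 72 h, can depend on how closely the SS was in touch with the woman.

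**4. How a death becomes known.** There are two routes: an SS report, or maternal recall at the final visit, which the evaluation team makes. The team's postnatal visits are not restricted to one arm.

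**5. What a gap in death capture would do (purely illustrative).** The plan's own ratio is 24.8/33 = 0.752. If the proportions of deaths captured are s_I in the intervention arm and s_C in control, observed ratio = 0.752 × s_I/s_C.

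- s_I = 1, s_C = 0.95: 0.752/0.95 = 0.791; s_C = 0.90: 0.835.
- s_C = 1, s_I = 0.95: 0.752 × 0.95 = 0.714; s_I = 0.90: 0.676.
- s_I = s_C: 0.752, no bias.

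The gap arises only among deaths that the evaluation visits miss. Let f be the share of deaths that depend on an SS report, and a and b the shares of these that the SS report in intervention and control. Then s_I/s_C = (1 − f + fa)/(1 − f + fb). With assumed a = 0.8 and b = 0.4:

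- f = 0: 0.752.
- f = 0.05: 0.752 × 0.99/0.97 = 0.767.
- f = 0.15: 0.752 × 0.97/0.91 = 0.801.

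With a and b exchanged, f = 0.05 gives 0.736 and f = 0.15 gives 0.705. None of f, a or b is in the article.

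**6. What a shift in recorded weight would do (purely illustrative).** With 15% low birth weight in control and an assumed normal distribution, a shift of d grams gives Φ(−1.036 − d/SD). For SD 400 g, d = 25 g gives 13.6% and d = 50 g gives 12.3%; for SD 450 g, 13.7% and 12.6%. A shift the other way gives 16.5% and 18.1% (SD 400 g), or 16.3% and 17.7% (SD 450 g). The planned effect is 15% to 10.5%. The shift and the SD are assumptions.

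**The case against.** The tempting stronger reading is that both outcomes are ascertained through the implementers, that deaths will be found more completely in the intervention arm, and that the primary effect is therefore biased towards no difference. The article does not support it, for these reasons.

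- Deaths are not found only through implementers. Maternal recall at the evaluation team's final visit is a full second route, and the same team also visits within 24 h and at 7–10 days. SS reporting supplements this follow-up and does not contradict it.
- The extra SS contact is documented only until delivery, before the neonatal period begins, and both arms receive BRAC postnatal care. Field Implementers appear to serve both arms.
- The direction is open. More contact could raise death capture in the intervention arm; reluctance of delivering staff to report deaths could lower it.
- It would also be tempting to size the bias by taking the 15% loss to follow-up in Sampling frame and sample size as infants missed at the 42-day visit. That figure is a general allowance in the recruitment yield and is not stated to mean this.

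On birth weight, it can be said that an electronic scale gives an objective reading, that the evaluation team's training covers standardised measurement, and that an article is condensed. The first two points lower the risk but do not settle who weighs or when. The third does not answer the point, because this is a conflict between sections and not an omission.

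**Conclusion.** The point holds as a conflict in the text on who collects birth weight, with a resulting risk that measurement and age at weighing differ by arm. That part needs no assumption beyond the wording, except that weighing by the SS or Field Implementer is implied and not stated. How far age at weighing matters also depends on how much weight changes over the first 72 h, for which the article gives no figure.

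For neonatal mortality the conclusion is weaker: SS reporting is an additional and possibly arm-dependent route, and bias is a risk, not a demonstrated fault. It is zero if the 42-day visit captures all deaths in both arms, and otherwise could run either way.

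The size is unknown for both outcomes. The illustrative figures show only that small gaps would matter if they existed; they are not estimates. The conflict is cheap to remove and should be removed before the outcomes are collected, but it does not by itself undermine the primary outcome as described.

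**What to change.** 1. Reconcile the Birth weight and Neonatal deaths sections with the three evaluation sections. State that the evaluation-team data collector, not the SS or Field Implementer, weighs the infant in both arms.
2. Record hours since birth at weighing, compare it by arm, and add a sensitivity analysis of low birth weight that accounts for it. This is still needed after step 1, because the birth alert still comes from the SS.
3. Have the evaluation team confirm vital status by the same procedure in both arms. Use SS and Field Implementer reports to trigger that confirmation.
4. Record the route by which each death was first found, and report a sensitivity analysis of neonatal mortality restricted to deaths found at evaluation-team visits.

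Removing deaths known only from SS reports from the primary analysis is not recommended, since it would discard true events; the restricted count belongs in the sensitivity analysis.

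The cost is some extra coordination between the two teams, a time field at weighing, a source field for each death, and two additional analyses. No new staff or visits are needed, because the evaluation team is already scheduled within 24 h and at 38–42 days.

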#### Duration of gestation

We will measure the duration of gestation will be measured using the date of last menstrual period with the pregnancy confirmed by urine test in the field.

#### Other measurements

Social, economic and demographic characteristics will be collected in a questionnaire collected at enrolment and will use standard demographic and health survey methods of an inventory of household assets to construct a wealth index, [16] as well as the socio-demographic characteristics of the mother.

#### Cost-effectiveness analysis

The economic evaluation will take a societal perspective. We will base the data for the cost-effectiveness analysis on the costs and outcomes observed in the trial. The costs of the intervention will include cost and distribution of the supplements, training of SS workers, organisational costs associated with the administration of the programme and the cost of incentives. We will ask the participants to record use of health services at each follow-up interview, which will enable assessment of potential cost offsets particularly associated with differences in rates of birth complications and neonatal morbidity. We will estimate incremental cost-effectiveness ratios as incremental cost per neonate death avoided; per low birth weight infant avoided and per life-year saved. Years of life saved will be based on any difference in survival of mothers and infants observed during the trial and estimated using current life expectancy in Bangladesh. Standard methods for estimating uncertainty and a cost-effectiveness acceptability curve will be generated to provide information on the probability that the intervention is cost-effective, at different willingness to pay thresholds.

#### Groundwater iron

We will measure the level of groundwater iron in all the households of our study using a validated test kit tool [±0.1 mg/L, FerroVer method, HACH Iron Test kit, Model IR-18B].

### Sampling frame and sample size

To detect a 25% reduction in neonatal mortality (33 neonatal deaths/1000 live births in control to 24.8 neonatal deaths/1000 live births in the intervention group), with 90% power, 5% two-sided alpha, 1:1 ratio of treatment allocation and intra-cluster correlation coefficient (ICC) of 0.0245, we require 100 clusters (each covering an average of 4000 households), or 50 clusters per treatment group, with a total of 30,000 live births over one year. This sample would allow detection of a 22% relative difference between treatment groups with 80% power. To detect a 30% reduction in preterm delivery from 15% in control compared to 10.5% in the intervention arm, assuming 80% power, 5% level of significance, intracluster correlation of 0.012 for small birth size (Bangladesh DHS data), would require a sample size of 1300/arm or 40 pregnant women from 64 clusters. A smaller sample size of 570 women/arm or 40 pregnant women from 28 clusters is needed to detect a 30% reduction in LBW with the same assumptions. Our cluster is one BRAC PO area that consists of ~ 13,000 people. Assuming a crude birth rate of 23 per 1000 people, 10% loss of pregnancies before birth and 15% loss to follow up each cluster will yield 300 births over 15 months, and this will be sufficient to reach the desired sample size.

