### Objectives and hypothesis

The trial objectives are to evaluate the effect of early availability and promotion of IFA supplements on neonatal mortality, low birthweight and preterm delivery. The primary hypothesis is that in a community-based, cluster randomized controlled trial of women from rural Bangladesh, daily supplementation with 60 mg elemental iron and 400 μg folic acid starting in the first trimester of pregnancy, and sustained for at least 180 days, will reduce neonatal mortality by 25% from 33/1000 to 24.8/1000 live births compared to usual iron-folic acid supplementation programs.

The secondary hypotheses are that the early availability and promotion of IFA supplements in intervention clusters will reduce preterm delivery by 30% (15% in control to 10.5% in intervention), and low birth weight by 30% (15% in control to 10.5% in intervention). We further hypothesised that household wealth and maternal education would modify the neonatal mortality responses with a greater reduction for women from the poorest households, and women with no education. We also hypothesised that the early start to IFA supplements would not increase iron-related side effects, e.g. nausea & vomiting in intervention clusters and will be cost-effective in reducing neonatal mortality in intervention clusters.

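### The printed ICC of 0.0245 is incompatible with the stated power: 100 clusters of 300 live births give about 31% power for the 25% reduction, not 90%

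*Protocol article*

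**What the plan says.** The section Sampling frame and sample size sets the primary comparison at "33 neonatal deaths/1000 live births in control to 24.8 neonatal deaths/1000 live births in the intervention group". The test is two-sided at 5%, the arms are of equal size, and the claimed power is 90%. The clustering input and the resulting size are given as "intra-cluster correlation coefficient (ICC) of 0.0245, we require 100 clusters (each covering an average of 4000 households), or 50 clusters per treatment group". The overall target is put at 30,000 live births in a year. A second claim is made for the same design: "This sample would allow detection of a 22% relative difference between treatment groups with 80% power". The section Objectives and hypothesis gives the same effect as the primary hypothesis, that supplementation "will reduce neonatal mortality by 25% from 33/1000 to 24.8/1000 live births".

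The cluster size is fixed by the document: 30,000 / 100 = 300 live births. The end of the sample size section arrives at the same 300 per cluster after allowing for pregnancy loss and loss to follow-up. No source is given for the mortality ICC, and no other ICC for mortality appears in the article. The ICC used for preterm delivery, by contrast, is attributed to Bangladesh DHS data.

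**The concern.** With 300 births per cluster, even a small ICC inflates the variance a great deal. At 0.0245 the inflation is more than eightfold, while 15,000 births per arm is less than twice the number needed with no clustering at all. The stated inputs therefore cannot lead to the stated 90%.

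This calculation is the article's only justification of the trial's size for its primary outcome. If 0.0245 was really the planning value, the trial would have less than a one-in-three chance of detecting its own hypothesised effect. If it is a misprint, the design may be sound, but the published coefficient is wrong by about a factor of ten, and anyone planning a later cluster trial of neonatal mortality could copy it.

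**Working it through.** **Inputs (all from Sampling frame and sample size).** p1 = 0.033, p2 = 0.0248, two-sided alpha 0.05, 1:1 allocation, 50 clusters and 15,000 live births per arm, m = 300 per cluster, ICC = 0.0245.

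**Method check on the plan's own preterm figure.** For 15% against 10.5% with 80% power, the pooled two-proportion formula gives 862 per arm. With 40 women per cluster and ICC 0.012, the design effect is 1 + 39 × 0.012 = 1.468, and 862 × 1.468 = 1,265 per arm (1,330 with continuity correction). The article states 1,300. The usual design effect, 1 + (m − 1) × ICC, is therefore a fair reading of the method used.

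**Births needed without clustering.** n per arm = (1.960 + 1.282)² × [0.033 × 0.967 + 0.0248 × 0.9752] / 0.0082² = 10.507 × 0.056096 / 0.00006724 ≈ 8,766. The pooled form gives 8,770.

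**Stated ICC, 0.0245.**
- Design effect = 1 + 299 × 0.0245 = 8.3255.
- Effective births per arm = 15,000 / 8.3255 ≈ 1,802.
- Standard error = √(0.056096 × 8.3255 / 15,000) = 0.00558; difference / SE = 0.0082 / 0.00558 = 1.47.
- Power = Φ(1.47 − 1.96) = Φ(−0.49) ≈ 31%.
- For a 22% reduction (0.033 to 0.02574), difference / SE = 0.00726 / 0.005624 = 1.29, and power ≈ 25%.
- Detectable reduction: about 45% at 80% power and 51% at 90%.
- Clusters for 90% power: 8,770 × 8.3255 / 300 = 243.4, so 244 per arm.

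**Can another reading rescue 90% at ICC 0.0245?**

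| Variant | Result |
|---|---|
| Exact 25% reduction (24.75 per 1000) | 31.5% power |
| t-test with 98 df | 30.7% power |
| One-sided 5% alpha | 43% power |
| Unlimited births per cluster (effective n = 50 / 0.0245 = 2,041) | 35% power |
| Clustering ignored | 98.9% power |
| 0.0245 read as a between-cluster coefficient of variation | about 31 clusters per arm, not 50 |

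None does. The fourth row is decisive: no cluster size lets 50 clusters per arm reach 90% at this ICC.

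**What ICC fits the stated design?** For 90% power at a 25% reduction, the largest allowable design effect is 15,000 / 8,770 = 1.710, so ICC = 0.710 / 299 = 0.0024. For 80% power at a 22% reduction, 8,490 births per arm are needed without clustering; 15,000 / 8,490 = 1.767, so ICC = 0.767 / 299 = 0.0026. The value 0.00245 lies between the two. It gives a design effect of 1 + 299 × 0.00245 = 1.7326. Power is then 89.6% with 24.8 per 1000 (90.0% with 24.75) and 81% for the 22% reduction, and 90% power needs 8,770 × 1.7326 / 300 = 50.6 clusters per arm.

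**Plausibility.** The between-cluster coefficient of variation implied at 3.3% mortality is √(ICC × 0.967 / 0.033): 0.85 for 0.0245 and 0.27 for 0.00245.

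**The case against.** The arithmetic is hard to dispute, so the best counter-argument concerns the diagnosis. The two stated powers agree with each other and with 100 clusters; only the printed ICC is out of line. On that view the design is adequate, and the 31% describes a trial that nobody planned. This stands as the likelier explanation, but the document cannot confirm it, and the figures as printed still contradict each other.

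A second point is that 0.00245 is not the only candidate. A between-cluster coefficient of variation of 0.245, mislabelled and shifted by one decimal place, gives about 46 clusters per arm for the 25% reduction at 90% power and about 45 for the 22% reduction at 80%, using the Hayes–Bennett formula. That could have been rounded up to 50. It corresponds to an ICC of about 0.0020 (0.245² × 0.033 / 0.967). This also stands, and it is why the correction must come from the source and not be inferred.

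Third, randomisation is stratified by Upazila (Assignment of treatments), which can remove some between-cluster variance. To reach 90% power, stratification would have to reduce the ICC from 0.0245 to about 0.0024, roughly a 90% cut. The article claims no such allowance.

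Finally, how informative a null result is will depend on the clustering actually observed and the resulting confidence interval, not on the planning ICC. That is correct. The error lies in the stated justification and does not by itself condemn the eventual result.

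**Conclusion.** The concern holds. With the printed inputs, power is about 31% for the 25% reduction (stated 90%) and about 25% for the 22% reduction (stated 80%), and no standard variant comes near the stated values. Either the ICC or the power statement is wrong. An ICC near 0.0024 to 0.0026 is what the stated design implies, which makes a misplaced decimal in 0.0245 the most probable cause, but that is an inference. The result rests on the usual design effect with equal clusters of 300 and makes no allowance for stratification.

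**What to change.** Trace the mortality ICC to its source, and cite that source in the sample size section.

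- If the source value is 0.00245, correct the figure and state the design effect (1.73) and the power: about 90% for the 25% reduction (89.6% with the rounded 24.8 per 1000) and 81% for the 22% reduction.
- If the source quantity is a between-cluster coefficient of variation, label it as such and name the formula used.
- If 0.0245 really was the planning value, withdraw both power statements. Replace them with about 31% for the 25% reduction, about 25% for the 22% reduction, and a detectable reduction of about 45% at 80% power.

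In no case should 0.0245 remain beside 90%. The cost is a source check and one corrected number or sentence. If the coefficient is a misprint, no cluster, participant or analysis changes. If it is not, the adequacy of the trial's size has to be reconsidered, since 90% power would take about 244 clusters per arm.

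### The low birth weight sample size of 570 per arm does not follow from the stated 15% to 10.5% hypothesis, which needs about 1,260 to 1,330 per arm

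*Protocol article*

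**What the plan says.** Objectives and hypothesis in the Protocol article sets two secondary hypotheses with identical numbers. Preterm delivery is to fall by 30%, from 15% to 10.5%, and so is "low birth weight by 30% (15% in control to 10.5% in intervention".

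Sampling frame and sample size treats the two outcomes in turn:

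- **Preterm delivery.** The target is given as "To detect a 30% reduction in preterm delivery from 15% in control compared to 10.5% in the intervention arm". The error rates are set by the words "assuming 80% power, 5% level of significance", and clustering enters through an "intracluster correlation of 0.012 for small birth size (Bangladesh DHS data". This, it says, "would require a sample size of 1300/arm or 40 pregnant women from 64 clusters".
- **LBW.** "A smaller sample size of 570 women/arm or 40 pregnant women from 28 clusters is needed to detect a 30% reduction in LBW", and the sentence ends by tying this to the preterm inputs: it "is needed to detect a 30% reduction in LBW with the same assumptions".

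The section gives no separate control risk, intracluster correlation, power or alpha for LBW. The only LBW risk in the article is the 15% in the hypothesis.

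**The concern.** The two outcomes share every input that the article states, yet the LBW size is less than half the preterm size (1,300 / 570 = 2.3). No choice of formula is needed to see that both sizes cannot follow from the same inputs.

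What is at stake is which hypothesis was planned. If the LBW size is wrong, anyone who relied on 28 clusters for LBW would have less than an even chance of detecting the stated effect. If the 15% is wrong, the published hypothesis misstates the expected control risk and the absolute effect. LBW is also a named secondary outcome and the basis of one of the cost-effectiveness ratios, so its expected risk should be stated correctly.

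**Working it through.** **Inputs**

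- Control and intervention risk: p1 = 0.15, p2 = 0.105 (Objectives and hypothesis, for both outcomes).
- Power 80%, alpha 5%, intracluster correlation 0.012, 40 women per cluster (Sampling frame and sample size).
- Sidedness is not repeated for the secondary outcomes. Two-sided is taken from the primary calculation in the same section ("5% two-sided alpha, 1:1 ratio of treatment allocation"); one-sided is tried below.

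**Step 1: reproduce the preterm figure**

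n per arm = (1.960 + 0.842)² × [p1(1 − p1) + p2(1 − p2)] / (p1 − p2)²
= (1.960 + 0.842)² × (0.1275 + 0.0940) / 0.045² = 858

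Design effect = 1 + (40 − 1) × 0.012 = 1.468

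| Variance formula | n before clustering | × 1.468 |
|---|---|---|
| Unpooled | 858 | 1,260 |
| Pooled | 862 | 1,266 |
| Pooled, continuity correction | 906 | 1,330 |

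The article states 1,300 (64 × 40 / 2 = 1,280 per arm). It is reproduced within about 3%, so this is in substance the method the authors used.

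**Step 2: apply it to LBW**

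The inputs are the same, so the answer is the same: 1,260 to 1,330 per arm, or about 32 to 34 clusters of 40 per arm. The article states 570 (28 × 40 / 2 = 560 per arm).

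**Step 3: look for any variant at 15% versus 10.5% that gives 570**

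| Variant | n per arm |
|---|---|
| One-sided alpha, clustered | 993 to 1,060 |
| Two-sided, clustering ignored | 858 to 862 |
| One-sided, clustering ignored | 676 to 679 |
| Two-sided, intracluster correlation 0.0245 (the primary outcome's value) | 1,686 |

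None reaches 570. Even with no clustering and a one-sided test the requirement is above 670.

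**Step 4: power at the stated size**

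Effective n = 570 / 1.468 = 388 per arm. Two-sided power for 15% versus 10.5% is 46.8% (46.1% at 560 per arm). It is 59.3% with one-sided alpha and 62.5% with two-sided alpha and clustering ignored.

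**Step 5: what inputs would give 570**

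- Keeping the 30% reduction and two-sided alpha: a control risk of 28.6% (unpooled), about 29% (pooled) or 30% (continuity correction, 571 per arm). The absolute reduction would then be 8.6 to 9.0 percentage points, not 4.5.
- Keeping 15% in control: a reduction of about 43% (574 per arm), not 30%.

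A one-sided test would fit a control risk of about 24 to 25.5%, but a one-sided test does not reproduce the preterm figure.

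**Step 6: the trial as planned**

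30,000 live births in 100 clusters is 15,000 per arm and 300 per cluster. Design effect = 1 + 299 × 0.012 = 4.588; effective n = 15,000 / 4.588 = 3,269 per arm; power for 15% versus 10.5% exceeds 99.9%. If only 40 infants were weighed in each of the 100 clusters (2,000 per arm, effective n = 2,000 / 1.468 = 1,362), power would be about 94%.

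**The case against.** There are three serious points on the other side.

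First, the 570 governs nothing. Neonatal mortality sets the trial size, no section plans a 28-cluster subsample for LBW, and Trial outcomes, Birth weight and Data collection schedule point to weighing births throughout the study area. This stands. The 47% describes the stated sample size, not the trial, and no estimate, test or recruitment target changes.

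Second, the shared assumptions may mean only power, alpha, intracluster correlation and cluster size. By calling the LBW sample smaller, the authors may show that they knowingly used a higher LBW control risk. On that reading the sample size section is coherent, and the slip is the LBW parenthesis in the hypothesis, which repeats the preterm figures. This is plausible and fits Step 5. It does not remove the error; it moves it to Objectives and hypothesis.

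Third, the risk of about 29 to 30% is back-solved, and a 43% reduction from 15% fits as well. This also stands. The stated 1,300 lies between the uncorrected and corrected results, so the exact formula cannot be identified. The authors must say what they used, and the inferred rate should not be written in for them.

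**Conclusion.** The point holds. The stated hypothesis of 15% to 10.5% and the stated LBW size of 570 per arm cannot both be right. Under the article's own inputs LBW needs 1,260 to 1,330 per arm, about 2.2 to 2.3 times the stated figure, and 570 gives about 47% power. These figures assume two-sided alpha, 40 women per cluster and an intracluster correlation of 0.012 for LBW; the contradiction itself depends on none of these, since both outcomes carry the same inputs.

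The document cannot settle which figure is wrong. The practical effect is limited: with all planned live births weighed the trial has ample power for LBW. It should be corrected because a pre-stated secondary hypothesis or its sample size is misreported.

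**What to change.** The authors should go back to the original LBW calculation and make the two sections agree, in one of two ways:

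- If 15% to 10.5% is the intended LBW hypothesis, replace 570 per arm and 28 clusters with the preterm requirement (about 1,300 per arm, 64 clusters of 40) and drop the statement that a smaller sample suffices.
- If a different control risk or effect was used for LBW, state it with its source in Sampling frame and sample size, and correct the LBW figures in Objectives and hypothesis to match.

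In either case, add one sentence saying that LBW is analysed on all weighed live births, with the power for that number. For 15% versus 10.5% with 15,000 weighed per arm it is above 99.9%; the figure should be recomputed if the control risk changes or fewer infants are expected to be weighed.

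The cost is a text correction of a few figures. Design, recruitment and analysis are unchanged.
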